**Objective:**

The objectives of this study are to (1) investigate the relationship between peer assessments of intraoperative technical skills and nontechnical practices with risk-adjusted complication rates and (2) evaluate the feasibility of using computer-based metrics to automate the assessment of important intraoperative technical skills and nontechnical practices.

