#### Peer Assessment Module

We will use a two-stage process for recruiting candidate assessors as follows: (1) we will poll the Michigan Society of Thoracic and Cardiovascular Surgeons Quality Collaborative (MSTCVS-QC), MPOG, and the Michigan Perfusion Society membership for potential assessors working outside of Michigan or at hospitals not participating in MPOG, and (2) if unable to secure sufficient assessors, we will recruit from the MSTCVS-QC, MPOG, and Michigan Perfusion Society membership.

Assessors, blinded to the hospital and operative team, will provide technical (aim 1) and nontechnical (aim 2) video-based assessments of cardiac surgical operations using a web-based Health Insurance Portability and Accountability Act (HIPAA)-compliant assessment platform.

Each operation will receive at least 12 assessments (three for each provider group), with 20% of assessments rereviewed. Surgeons will assess a surgeon’s (1) technical skills (modified OSATS plus cardiac surgery–specific skills) via a validated 5-point behaviorally anchored scale and (2) nontechnical practices using NOTSS [13]. Anesthesiologists will use ANTS [14], scrub nurses will use SPLINTS [15], and perfusionists will use PINTS for nontechnical assessments (all nontechnical taxonomies will use an 8-point ordinal scale). Segments will capture each operation’s critical phases. Technical skill assessors will be given one operative field camera angle (Cam Surgical Field [SF]) for their assessment (Figure 2). Given the interdependence of intraoperative team members, nontechnical assessors will be provided alternative camera angles depicting the intraoperative team (Cam Operative Team [OT] #1 and #2). Assessors will receive an Amazon coupon for completed reviews.

We will resubmit 20% of edited segments to the same (test-retest reliability) or other assessors (interrater reliability) using an intraclass correlation coefficient α ≥.670 for good concordance [28].

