### Aim 3: Explore the Feasibility of Using Objective, Data-Driven, Computer-Based Assessments to Automate the Identification and Tracking of Significant Intraoperative Determinants of Risk-Adjusted Patient Adverse Events

High-dimensional computer-based assessments of digital recordings will be used to recognize and track human activity (computer vision). Computer vision focuses on training computers to derive meaning from visual imagery. Video understanding, a specialty within computer vision, focuses on identifying and tracking objects over time from video and developing mathematical models to train computers to extract the meaning within these moving images. This field may offer unparalleled capabilities for conducting objective peer assessments by automatically identifying and tracking human activity comparable to that of expert human assessors.

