#### Measures

Our primary outcome will be the features derived from the video-understanding platform, which will be compared to a gold standard human identifying the same features. Features, as economy of motion, are derived from the raw output of the video-understanding platform, which naturally performs visual detection and visual tracking. The gold standard uses the analogous “raw output” from humans and the same method for the computation of the derived feature.

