#### Analytical Plan

We will assess our video-understanding platform’s ability to correctly identify and track features within our testing data set. Using the raw video in the testing set, we will provide the necessary bounding-box annotations for each feature, which will be compared to the automatically generated features from the video-understanding system using standard metrics (eg, intersection over union [44] and DICE coefficient [45]). For example, when we compute the economy of motion of the surgeon’s hand, we will provide bounding-box annotations of the surgeon’s hand. The video-understanding system will use these annotations to learn a mathematical visual detection model capable of producing the detections of the hand on novel video. Thereafter, the economy of motion feature will be derived on the output bounding boxes. We plan a two-phased analysis. First, we will measure agreement and associate each feature with each component of the technical and nontechnical assessments (specific to each operative phase) using Pearson/Spearman correlation coefficients or Kendall tau, depending on data distribution. Second, we will identify the best combination of video-understanding features that are most closely associated with technical and nontechnical score domains (specific to each operative phase). We will use regression (eg, linear, ridge, and deep) to model each domain and technical and nontechnical summary scores as dependent variables, including features from the video-understanding platform as independent variables. We will (1) select features using variable selection and (2) quantify the magnitude of information in peer assessment that can be identified by the computer using generalized R squares.

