## Results

The project has been funded by the National Heart, Lung and Blood Institute in 2019 (R01HL146619). Results of aims 1 and 2 will likely yield assessments that identify a wide range of variations in both surgeons’ technical skills and nontechnical practices as has already been documented in the literature. Where our study will make an important contribution is in associating these assessments with adverse event rates. The novel contribution of aim 3 will be to associate computer-based assessments with adverse event rates, as a more objective and reliable replacement for human peer assessors, moving us closer to our overall goal of improving outcomes for cardiac surgery patients. We will use the study results to develop data-driven technical skills and nontechnical practice coaching interventions across a subset of hospitals. We plan to undertake our study over a 5-year period (Figure 3).

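### Aim 3 never sets the computer beside assessor-to-assessor agreement, so its correlations and R-squares cannot support the replacement statement in the Results section

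*Protocol article*

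**What the plan says.** The formal objective is to "evaluate the feasibility of using computer-based metrics to automate the assessment of important intraoperative technical skills and nontechnical practices". The introduction to Aim 3 says that the field of video understanding may offer capabilities for "automatically identifying and tracking human activity comparable to that of expert human assessors". The Results section goes further and describes the Aim 3 contribution "as a more objective and reliable replacement for human peer assessors".

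The planned evaluation, in the Aim 3 Measures and Analytical Plan, has three parts:

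- Platform features are "compared to a gold standard human identifying the same features", using overlap measures such as intersection over union and the Dice coefficient.
- Each feature is correlated with each component of the peer assessments (Pearson, Spearman or Kendall), by operative phase.
- Peer domain and summary scores are regressed on the features with variable selection, to "quantify the magnitude of information in peer assessment that can be identified by the computer using generalized R squares".

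The Peer Assessment Module gives each operation three assessments per professional group and judges rater reliability "using an intraclass correlation coefficient α ≥.670 for good concordance". The Aim 1 Analytical Plan also estimates an interassessor ICC. The Aim 3 Analytical Plan uses neither.

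**The concern.** To call the computer a more reliable replacement for peer assessors, one needs to know how well a peer assessor does. None of the three planned analyses supplies that. Box overlap tests whether the platform finds the same objects as a human annotator, which is a different task from rating skill. The correlations and the R-square do relate the platform to peer scores, but without a human reference value beside them.

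The plan also reads the R-square as the amount of peer-assessment information that the computer recovers. Observed peer scores contain assessor error, which video features cannot be expected to recover, so 1 is not the attainable maximum. The maximum depends on the reliability of the score, which may differ by domain, scale and phase. Raw values could then rank domains partly by rater noise, and a platform that performs like a human could look weak or strong depending on how well the raters agree.

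**Working it through.** Aim 3 states no target R-square, sample size or power, so there is no figure to reproduce. The check asks how much a raw R-square can be read without a reference value.

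**Inputs from the article:** three assessors per professional group for each operation; an ICC threshold of 0.670 (Peer Assessment Module); 506 recorded operations and 36 surgeons. **Assumptions:** the operation is the unit, assessor errors are independent, and 0.67 is a single-assessor ICC. The range 0.4 to 0.8 is also an assumption.

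**Formulas**, with ρ the single-assessor ICC:

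- Reliability of the mean of k assessors (Spearman-Brown): Rel(k) = kρ / (1 + (k − 1)ρ). This is the R-square ceiling for a perfect measure of the error-free score. The ceiling for a Pearson correlation is its square root.
- Human benchmark, as the squared correlation of one assessor with the mean of two others: ρ × Rel(2).

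**At ρ = 0.67:**

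- Rel(3) = 2.01 / 2.34 = 0.859, so a correlation is capped at √0.859 = 0.927.
- Rel(2) = 1.34 / 1.67 = 0.802.
- Human benchmark = 0.67 × 0.802 = 0.538.

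| Single-assessor ICC | Ceiling, mean of three | Ceiling, mean of two | One assessor vs mean of two others |
|---|---|---|---|
| 0.40 | 0.667 | 0.571 | 0.229 |
| 0.67 | 0.859 | 0.802 | 0.538 |
| 0.80 | 0.923 | 0.889 | 0.711 |

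**What a raw value means.** A platform R-square of 0.50 against a two-assessor mean is well above one human at ICC 0.40, slightly below at 0.67 and well below at 0.80.

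**Comparability across domains.** Suppose the platform explains 0.60 of the error-free score in two domains. On a three-assessor mean this appears as 0.60 × 0.667 = 0.40 where the ICC is 0.40, and as 0.60 × 0.923 = 0.55 where it is 0.80.

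**If 0.67 is the reliability of the three-assessor mean:** ρ = 0.67 / (3 − 2 × 0.67) = 0.404. The three-assessor ceiling is then 0.67. Rel(2) = 0.808 / 1.404 = 0.575, and the human benchmark is 0.404 × 0.575 = 0.23.

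**A force in the other direction.** The plan selects variables before computing the R-square and states no hold-out for this regression. A simulation used ICC 0.67, a three-assessor mean, 300 replicates and assumed feature counts (10 selected from 30, or 15 from 60). With an error-free R-square of 0.60, the expected observed value is 0.60 × 0.859 = 0.515. The mean in-sample R-square was 0.68 to 0.78 with 36 units, 0.58 to 0.63 with 100, and 0.53 to 0.54 with 506. With no true signal it was 0.49 to 0.69, 0.22 to 0.34 and 0.05 to 0.08.

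**The case against.** The strongest reply is that Aim 3 only explores feasibility. Its declared primary outcome is platform features against a human identifying the same features, and box overlap fits that outcome. The comparability remark in the Aim 3 introduction describes the field, not a study hypothesis. The replacement wording is in a forward-looking Results sentence about associating computer-based assessments with adverse event rates. All of this stands. A reader might infer that Aim 3 formally tests whether the computer can replace an assessor. The documents state no such hypothesis. The mismatch is between the Results statement and the Aim 3 analyses.

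A reader might also infer that the R-square is simply biased low. That does not follow. As a share of variance in observed peer scores it is capped by reliability, not biased by it; it is attenuated only as a measure of the error-free score. In-sample fitting after variable selection pushes the other way, so the net direction is open.

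The size is also conditional. The 0.670 is a minimum, and the article does not say whether it applies to one assessor or to a mean. Aim 1 summarises technical skill by surgeon-level model predictions. With 506 / 36 ≈ 14 operations per surgeon, rater error in such summaries would be averaged further and the ceiling would be higher.

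Finally, the ICCs will be estimated, so a reader could place them beside the R-square, and an analysis plan not shown may specify a hold-out or a benchmark. This lowers the weight of the point but does not remove it, because the article itself fixes both the metric and its reading.

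**Conclusion.** The point holds as a limit on interpretation. The planned overlap measures, correlations and R-squares can inform feasibility. Without a human benchmark they cannot show that the platform is comparable to a peer assessor or more reliable than one, and raw values should not be compared across domains or phases with different rater reliability.

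With the operation as unit and 0.67 as a single-assessor ICC, a perfect platform would reach at most 0.86 on a three-assessor mean, and a platform equal to one assessor would show about 0.54 against the mean of two others. Over assumed ICCs of 0.4 to 0.8 the ranges are 0.67 to 0.92 and 0.23 to 0.71. These figures are illustrations: surgeon-level summaries would raise the ceiling, and in-sample selection can inflate the R-square. Aims 1 and 2 are not affected.

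**What to change.** In the Aim 3 Analytical Plan:

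1. Estimate the platform's agreement with peer scores out of sample, with folds by surgeon and with variable selection repeated inside each fold.
2. For each domain, summary score and phase, report the platform's agreement with the mean of two assessors beside the same statistic for the left-out third assessor, rotating over the three. Give the difference with an interval clustered by surgeon.
3. Report the ICC-based ceiling beside each R-square or correlation, and state the unit of analysis and whether the ICC refers to one assessor or to a mean.
4. Base any comparability or replacement statement on step 2. Otherwise limit the Results sentence to feasibility.

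The three assessments per professional group and the ICCs are already planned, so no new ratings or recordings are needed. The cost is a little extra analysis, plus the added uncertainty from the estimated ICC in the ceiling and in any reliability-corrected R-square.

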## Results

The project has been funded by the National Heart, Lung and Blood Institute in 2019 (R01HL146619). Results of aims 1 and 2 will likely yield assessments that identify a wide range of variations in both surgeons’ technical skills and nontechnical practices as has already been documented in the literature. Where our study will make an important contribution is in associating these assessments with adverse event rates. The novel contribution of aim 3 will be to associate computer-based assessments with adverse event rates, as a more objective and reliable replacement for human peer assessors, moving us closer to our overall goal of improving outcomes for cardiac surgery patients. We will use the study results to develop data-driven technical skills and nontechnical practice coaching interventions across a subset of hospitals. We plan to undertake our study over a 5-year period (Figure 3).

**Figure 3 figure3:**

Study timeline.

## Discussion

### Strengths

There is increasing demand from the public and payers to improve health care value (quality divided by expenditures). Despite wide variability in cardiac surgical quality and robust clinical data from the STS for risk adjustment and outcomes ascertainment, only 2% of hospital variability in some outcomes are explainable by currently recorded data elements [46]. Analysis of operative videos may reveal unique opportunities for advancing operative quality improvement beyond that provided through traditional data sources [47].

Our proposed study, leveraging the infrastructure and track record of two established physician-led quality collaboratives integrated with a cutting-edge scalable video-understanding platform, will advance our understanding of how surgical skills and nontechnical practices impact outcomes. Our approach aimed at identifying key modifiable intraoperative determinants of major adverse events may likely be applied to approximately 200,000 additional cardiac surgical procedures involving valve repair or replacement, aortic procedures, and percutaneous cardiac procedures (eg, transcatheter aortic valve replacement) or other high-risk noncardiac surgical specialties (eg, neurosurgery, orthopedics, and head and neck reconstructive surgery).

### Limitations

Although unlikely, there are a few potential challenges with this study.

#### Aims 1 and 2

There is a remote possibility that we will not find that the investigated technical skills are associated with adverse events. If needed, we will expand our review of surgical operations to include (1) hospitals with lower operative volume, (2) longer segments for peer rating, (3) an expanded list of operative phases that might distinguish between high- and low-performing surgeons, and (4) high-risk or technically challenging operations. We will consider expanding to other hospitals if (1) hospital variability in adjusted adverse events is less than anticipated or (2) we are unable to amass sufficient digital recordings from our initial six hospitals.

If needed, we will (1) expand our sampling pool of assessors to include providers who have expressed desire to partner on this project but were not selected initially, (2) provide monthly feedback and engagement support to participating assessors, and (3) provide expanded assessor training and calibration.

#### Aim 3

Our video-understanding platform may not be completely automated. Alternatively, we will consider a semiautomated platform that relies, for instance, on a human periodically manually annotating the relevant features in the video at a certain segment and then allowing the video-understanding platform to interpolate those annotations.

## Abbreviations

ANTS: Anesthetists’ Non-Technical Skills
CABG: coronary artery bypass grafting
DCC: Data Coordinating Center
HIPAA: Health Insurance Portability and Accountability Act
MPOG: Multicenter Perioperative Outcomes Group
MSTCVS-QC: Michigan Society of Thoracic and Cardiovascular Surgeons Quality Collaborative
NOTSS: Non-Technical Skills for Surgeons
OSATS: Objective Structured Assessment of Technical Skill
OT: operative team
PINTS: Perfusionists Intraoperative Non-Technical Skills
SF: surgical field
SPLINTS: Scrub Practitioners’ List of Intraoperative Non-Technical Skills
STS: Society of Thoracic Surgeons
